## Abstract

**Background:**

The presence of mild cognitive impairment (MCI) in older adults increases their fall risk. While physical exercise is effective in reducing falls rate and risk of falls, and cognitive training in improving cognitive functioning in healthy older adults, their effectiveness in preventing falls and reducing risks of falls in MCI when administered simultaneously is not yet established. Therefore, this study aims to determine the effectiveness of combined physical and cognitive training in preventing falls and decreasing risks of falls among community-dwelling older persons with MCI.

**Methods/design:**

This is a single-blind, multicentre, randomized controlled trial. At least ninety-three community-dwelling older adults with MCI aged 60 or above will be recruited. They will be randomly allocated into four groups: Physical Training alone (PT), Cognitive Training alone (CT), combined Physical And Cognitive Training (PACT) and Waitlist Group (WG). The PT group will perform exercises (flexibility, endurance, strengthening, and balance training) for 60–90 min three times per week for 12 weeks. The CT group will be involved in a paper-based training focusing on orientation, memory, attention and executive functioning for 60–90 min per session, once a week for 12 weeks. The PACT group will undergo cognitive training incorporated in physical exercise for 60–90 min three times per week for 12 weeks. The WG will receive the intervention, combined physical and cognitive training, at a later date. Assessors blinded to participant allocation will conduct pre-intervention, post-intervention, and 6-month follow-up assessments. The primary outcome measure will be falls rate. The secondary outcome measures will be Physiologic Profile Assessment and Falls Risk for Older Persons in the Community, and assessments that evaluate cognitive, physical and psychological factors related to falls.

**Discussion:**

Considering the possible physical, social, financial and psychological consequences of a fall, we hope to provide insights on the effectiveness of combining physical and cognitive training on falls and fall-related factors for older adults with MCI. It is projected that the combined interventions will lead to significantly lower falls rate and reduced risk of falls compared to using single or no intervention.

**Trial registration:**

ClinicalTrials.gov NCT03167840. Registered on May 30, 2017.

## Background

Mild cognitive impairment (MCI) is associated with falls in the geriatric population [1], particularly among female older adults [2]. It is the intermediary state of cognitive decline between the changes due to the normal aging process, and the deterioration due to dementia and other neurological diseases [3]. The estimated global prevalence rate of MCI is between 5.0 and 36.7% [4].

MCI is considered a predictor of falls [5] but it is also a potentially ameliorable fall risk factor [6]. Interventions, including physical exercise and cognitive training [7], may be provided to address the decline in cognitive function and also the presence of some physical fall-related risk factors such as decreased balance control [8], muscle weakness [9] and slow gait [10] that predisposes older adults to incur a fall.

### Physical training

Physical exercise is one of the most common interventions used to prevent falls in the geriatric population [11, 12]. Exercise as a single intervention or as a component of a multifactorial intervention has been proven effective in reducing rate of falls and risk of falls among the general population of older adults living in the community [11, 12]. To successfully reduce falls incidence in older people, a minimum of three hours every week [11] for at least 40 h of exercise over the course of interventions is needed [13]. The optimal exercise frequency is purported to be three times per week [13]. Designing the program to comprehensively include balance, strength, endurance, and flexibility, but with at least one-third is focused on balance training, is recommended [11–13].

For community-dwelling older adults with cognitive impairment, there is promising evidence that exercise as a standalone intervention may prevent the occurrence of falls, however, this entails confirmation with more trials [11]. Older adults with MCI, in particular, are faced with certain cognitive hindrances when engaging in exercise such as learning new routines and remembering how to perform them accurately [14]. These cognitive obstacles were observed in spite of previous involvement in similar exercise regimens [15].

In terms of the effect of exercise on cognitive function, contrasting findings were reported. One meta-analysis concluded that there is very limited evidence that exercise improves cognitive function in MCI [16]. A more recent systematic review, however, reported positive effects of exercise on global cognition, executive function, attention and delayed recall in older persons with MCI [17]. Specifically engaging in aerobic exercise (walking, dancing, jogging, Tai Chi) at 60–80% maximum heart rate or > 3 metabolic equivalents has resulted to improved cognitive ability of older adults with MCI [18]. On the other hand, doing functional tasks as a form of exercise has been found to provide cost-effective and sustainable improvements in global cognitive function, memory and executive function in community-dwelling older persons with MCI [19]. These benefits were obtained with the use of physical exercise alone and without formal cognitive training of the participants.

### Cognitive training

Cognitive training, which usually involves guided practice on a set of specific tasks designed to solicit targeted cognitive functions [20], has been proven effective in healthy older adults in improving cognitive functioning [21–23] and may also be an effective preventive strategy in the onset of any cognitive decline among older persons [24]. Impairment in executive function is found to be independently associated with a heightened risk for falls and fall-related injuries in community-dwelling older adults [25, 26]. Executive function (EF) is a high-level subcomponent of cognition that regulates processes including working memory, inhibition and cognitive flexibility which are important in adapting efficiently to changing environment and task [27]. Targeting particularly executive dysfunction in cognitive training has been recommended to decrease the rate of falling in the geriatric population with cognitive impairment due to Alzheimer’s disease [28]. This strategy may help decrease falls rate in Alzheimer’s disease by addressing the perceptual-motor integration problem that causes instability in performing certain automatic tasks such as walking that eventually results in a fall [29].

In older adults with MCI, cognitive training has resulted in beneficial effects on cognitive function such as attention, orientation, perception, language, memory and executive function [23, 29]. However, there are a lot of inconsistencies in terms of the format (group versus individual), number and duration of treatment sessions in the previously implemented programs [23, 30]. It was found out that there is no dose-response relationship between the total training hours and the effectiveness of intervention on cognitive outcomes [23]. But, it seems that fewer sessions, about 6–20 sessions only, are considered more cost-effective [30]. Furthermore, cognitive training greater than 12 weeks duration did not show better outcomes compared to programs with ≤12 weeks duration, where the risk of attrition is also reduced [30].

### Combined physical and cognitive training

A treatment paradigm that could potentially address both cognitive decline and risk of falls in MCI is to combine physical exercise and cognitive training. Neuroplastic changes in the brain may be more evident if these two interventions are integrated. In an animal study, it was suggested that physical activity and cognitive stimulus had a complementary effect on neurogenesis [31]. In humans, combined physical/cognitive training had an effect on brain functional plasticity. The Train the Brain Consortium (2017) reported that there were lesser neural resources utilized, which means better neural efficiency, for the same behavioral activities in older individuals with MCI on combined interventions training compared to those without training [32]. Aside from neural efficiency, increased cerebral blood flow in the parahippocampal area in the medial temporal lobe of the brain was more evident after combined interventions. This area of the brain subserves non-verbal spatial information processing [32].

Among healthy older adults, combined interventions in the form of stationary cycling with virtual reality [33], and integrated aerobic exercise and mental training [34] resulted in better effects in their cognitive performance compared when the interventions were delivered separately. Similarly, progressive balance training with dual and multi-task exercises lead to positive short and long-term benefits in gait, balance control and fear of falling among community-dwelling healthy older adults with increased risk of falling [35].

For older adults with cognitive impairment, the effect of combined physical and cognitive training is rather inconsistent. In older persons with Parkinson’s disease, the multimodal cognitive program, including cognition, transfer training, psychomotor and endurance, had superior effects in cognitive function compared to paper-and-pencil-based cognitive training only [36]. In older adults with MCI, cognitive status was significantly improved following a 7-month combined physical-cognitive training and music therapy compared to no training [32]. Simultaneous physical and cognitive training by dual-tasking in older persons with MCI also resulted in significantly better cognitive outcomes compared to a waitlist group [37] or an education control group [38].

On the contrary, a study that combined resistance training and cognitive training in older adults with MCI concluded that doing high-intensity resistive training alone for six months lead to significant increase in global cognitive function, memory and executive function while participating in combined training unexpectedly and significantly reduced the benefits of isolated progressive resistance training on executive and global cognitive function [39]. In another study also involving older persons with MCI, dual modality cognitive-physical training and single modality interventions of cognitive training alone or physical exercise alone resulted in no significant differences in cognitive outcome measures [40]. In a systematic review, both older adults with and without cognitive impairment gained improvements in cognitive functions and functional status from combined physical exercise and cognitive training interventions [41]. However, the evidence is lacking to ascertain the superiority of combined interventions when compared to active control groups. More studies with good methodological quality are warranted to explore the potential benefits of this new treatment approach [41].

The link connecting the improvements in cognitive function and physical factors after undergoing physical exercise and cognitive training, singly delivered or in combination, to the reduction of falls and the decrease in falls risk in the geriatric population, particularly to those with MCI, is yet to be established.

Thus, this study primarily aims to determine the effectiveness of combined physical and cognitive training on preventing falls and reducing the risk of falls among community-dwelling older adults with MCI. The hypothesis is that an intervention that incorporates elements of both physical exercise and cognitive training in one treatment program is more effective compared to physical exercise or cognitive training alone in preventing the occurrence of falls and in decreasing the risk of falls in older adults with MCI living in the community.

## Methods

### Participants

Community-dwelling older adults, both male and female, aged 60 or above with MCI will be included. They will be recruited from community sites in Manila, Philippines through the assistance of local coordinators of the Office of Senior Citizens Affairs (OSCA) of Manila. The presence of MCI will be established following the criteria of Winblad et al. (2004) [42]. A person is diagnosed to have MCI if 1) the cognitive function is not normal nor demented; 2) there is subjective report of the individual and/or informant on declining cognitive function compared to five years ago [5] on objective cognitive tasks; and 3) the performance of basic ADLs is preserved with only minor problems doing complex instrumental ADLs [42]. Not normal cognitive function or presence of mild impairment will be based on Montreal Cognitive Assessment (MoCA) score of < 26 [43]. Not demented will be based on not having a medical diagnosis of dementia or Alzheimer’s disease [5, 44]. Normal function in ADL and no or minimal impairment in instrumental ADL will be based on Katz ADL Scale [45] and Lawton Instrumental Activities of Daily Living (IADL) Scale [4]. A trained neurologist-psychiatrist will examine the participants to provide the final diagnosis of MCI and give them the clearance to participate in the exercise. Only ambulatory older adults, with or without an assistive device, will be included since the interventions are community-based.

Older adults will be excluded if they have a diagnosis of dementia or Alzheimer’s disease; had history of major medical conditions such as cerebrovascular disease, cardiopulmonary condition, serious musculoskeletal disease, cancer, major psychiatric condition; have severe visual and/or hearing impairment; or are illiterate that will hinder them in participating fully and safely in the exercise and/or cognitive training programs. Furthermore, those who have been taking medications such as sedatives, antidepressants, diuretics, anti-epilepsy that might affect their cognitive function will not be included. Deliberately providing false information is a reason for termination of participation. Elevation of blood pressure beyond the expected increase due to exercise or the presence of fever and body pains for several days due to other causes may be reasons for withdrawal to participate. To enhance adherence to the intervention, participants will be receiving a travel allowance and light refreshments every time they attend sessions.

### Study design and procedures

This proposed study is a randomized controlled trial using a 4-group design including three intervention groups (physical training alone or cognitive training alone, or combined physical and cognitive training) and one waitlist control group. The study will comply with the principles of the Declaration of Helsinki 2013 and Good Clinical Practice Guidelines. Ethics approval was secured from the Human Subjects Ethics Sub-committee of the Hong Kong Polytechnic University-Department of Rehabilitation Sciences (HSEARS20170402001) and the Ethics Review Committee of the University of Santo Tomas-College of Rehabilitation Sciences (FI-2017-002). The SPIRIT guidelines were followed in the design of this study protocol.

Trained study personnel will interview the participants using questionnaires to obtain their demographic information and medical history, physical activity level and history of falls, and will conduct cognitive and physical performance tests to determine their eligibility to participate in this study. Only those who signed the informed consent will be included in this study.

Random allocation will be carried out by a third party not involved in the study by random draw to blindly allocate each participant to one of the four groups. To minimize experimental contamination through social interaction and communication among the participants, the interventions will be delivered at different sites.

Measurement points include baseline/pre-intervention, post-intervention, and six months follow-up assessments and will be conducted by trained study personnel blinded to the randomization assignment. Physiotherapists and occupational therapists who will be administering the interventions will not be involved in the outcome assessment. They will also have workshops and discussions to standardize the administration of the different training programs. After the intervention period, aside from a calendar-diary, monthly phone calls will also be done to follow up the participants about their fall status, physical activity, and exercise behavior. Figure 1 illustrates the study flow. Appendix shows the timeline of the study.

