### Sample size computation

The sample size and power calculations will be based on fall rate which is the primary outcome of the study. Using statistical software Gpower 3.1.9.2, a priori power analysis was conducted using the computed effect size (Cohen’s d = .39) from Trombetti et al. (2011) [46]. Assuming 80% power with 5% Type 1 error and four groups, the calculated total sample size is 80. Considering a 16% dropout rate (Trombetti et al., 2011) [46], the total number of participants is inflated to 93. There should be at least 23 participants per group.

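### The random draw should be stated as balanced and stratified by fall history: drawn independently, 93 people give at least 23 in every arm in only 0.44% of draws

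*Protocol article*

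**What the plan says.** Under Study design and procedures, the trial is a "randomized controlled trial using a 4-group design". A third party outside the study carries out the allocation "by random draw to blindly allocate each participant to one of the four groups". That section mentions no fixed lots, blocks, quotas or strata, and does not say that the draws are independent either.

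Under Sample size computation, 80 people are required, "the total number of participants is inflated to 93" for a 16% dropout, and the section adds: "There should be at least 23 participants per group". The abstract treats the total as a minimum: "At least ninety-three community-dwelling older adults with MCI aged 60 or above will be recruited".

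The interview that decides eligibility, and so precedes allocation, records "physical activity level and history of falls". The FROP-Com Screen, also taken at baseline, has an item on the number of falls in the past 12 months. The appendix timeline puts baseline assessment in August–September 2017 and randomisation in September 2017.

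Under Statistical analysis, fall rates are compared between groups by an incidence rate ratio. No use of baseline fall history is stated.

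**The concern.** The article fixes a minimum arm size with almost no slack and describes an allocation method without the feature that would secure it. Read plainly, a draw made for each participant is simple randomisation, and arm sizes then vary by chance. That affects more than the power calculation. The three training arms are delivered at different sites with one therapist per five participants, so site capacity and staffing depend on arm sizes.

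The second part concerns the primary outcome, falls rate. Fall history is a likely prognostic factor for it and is known before anyone is allocated. With about 23 people per arm, a visible imbalance in prior fallers between some arms is an ordinary chance event. As described, neither the design nor the falls comparison would absorb it.

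**Working it through.** **Inputs.** From Sample size computation: 80 people before dropout, 16% dropout, four groups, 93 in total, at least 23 per group. From the abstract: 93 is a floor. Equal allocation is implied by the per-group figure. The share of prior fallers is not in the document; 20–40% is assumed.

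**The plan's own figures.** 80 × 1.16 = 92.8, rounded to 93; 93 / 4 = 23.25, giving 23 per group. Both reproduce.

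**Arm sizes under independent draws.** Because 93 = 4 × 23 + 1, all arms reach 23 only if the sizes are 24/23/23/23, in one of four orders. So

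P(all ≥ 23) = 4 × 93! / (24! × 23!³) / 4⁹³ = 0.0044, or 0.44%.

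A simulation of 400,000 allocations gives 0.45%. The smallest arm has median 19 (95% range 13–22), the largest has median 28 (25–34), and the median gap is 10. At one therapist per five, an arm of 19 needs 4 therapists and an arm of 28 needs 6.

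**Does recruiting more than 93 help?** The same probability for larger totals:

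| Total | P(all arms ≥ 23) |
|---|---|
| 93 | 0.44% |
| 96 | 3.4% |
| 100 | 12.8% |
| 110 | 50.1% |
| 120 | 79.0% |

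**Arm sizes under fixed lots.** If 93 lots are prepared as 24/23/23/23, the minimum is met with probability 1.

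**Efficiency lost to unequal sizes.** Relative efficiency is 1 / (mean of 1/nᵢ × 93/4). Averaged over the simulated allocations it is 0.967, a loss of about 3%.

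**Fall history left to chance.** Take four equal arms of 23 (92 people) and distribute the prior fallers among them at random, 200,000 times. Since 4/23 is 17.4 points and 5/23 is 21.7 points, a gap of 20 points or more means at least five people.

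| Assumed prior fallers | Some pair differs by ≥ 20 points | Some pair differs by ≥ 30 points | One given pair differs by ≥ 20 points |
|---|---|---|---|
| 20% | 34% | 7% | 9% |
| 30% | 48% | 16% | 15% |
| 40% | 53% | 21% | 18% |

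Arm sizes are already equal here, so fixing the sizes alone does not remove this imbalance.

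**Do ordinary blocks within strata secure the minimum?** Not by themselves. Splitting 93 people into two strata with blocks of four leaves remainders of (0,1), (1,0), (2,3) or (3,2). In the last two cases, one arm misses out in the stratum with remainder 3. It falls to 22 unless it is among the two arms served in the other stratum, which has probability 2/4. The last two cases arise about half the time, so the minimum fails in about 1/2 × 1/2 = 25% of trials. Example with 27 fallers and 66 non-fallers: fallers split 7/7/7/6. Non-fallers split 17/16/16/17 give 24/23/23/23, but 17/17/16/16 give 24/24/23/22. The leftover lots must therefore be coordinated across strata.

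**The case against.** The strongest reply is that the article never calls the draw unrestricted. Drawing from a bowl of 93 prepared lots is also a random draw, always meets the minimum, and is consistent with the sample size section. A journal article may leave lot composition, block sizes and strata to the full protocol. This stands in part. A reader might infer that the plan contradicts itself, with a method that almost never yields its own arm sizes. The text does not support that: the 0.44% holds only for independent draws at exactly 93, and the article neither states independent draws nor caps the total at 93.

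A reader might also infer one randomisation session held after all baseline data were in. The timeline does not say so: baseline assessment and randomisation both include September 2017. What is supported is narrower: fall history is taken at the eligibility interview, hence before each person's allocation.

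Thirdly, simple randomisation is valid, the size penalty is about 3%, the imbalance figures rest on an assumed prevalence, and a given pair of arms is affected far less often than some pair. Adjustment may also be specified in an analysis plan that is not shown. These points limit the severity. They do not remove the value of using, in the draw and in the comparison, a baseline value that is already collected.

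**Conclusion.** The concern holds in conditional form. The article states no balancing for a draw that must give at least 23 per arm with one person to spare. If each person is drawn independently, the minimum is met in 0.44% of draws at 93 and 12.8% at 100; if fixed lots are drawn, it is always met. The document does not settle which applies.

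Fall history is available before allocation but is used in neither the stated draw nor the stated falls comparison. Under an assumed 20–40% prior fallers, some pair of arms differs by 20 points or more in 34–53% of trials. It would be tempting to call this bias. It is not bias in expectation, because random allocation remains valid; the cost is precision and credibility in a small four-arm trial. The improvement is worth making because it is nearly free, not because the design fails without it.

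**What to change.** In Study design and procedures, state that the third party draws, with concealment, from a prepared set of lots with fixed equal numbers per arm (for 93 people: 24/23/23/23). Stratify the lots by any fall in the past 12 months (yes or no), and coordinate the leftover lots across the two strata so that every arm reaches 23. If fixed lots were always intended, the first part is only a clarifying sentence.

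In Statistical analysis, state that the falls-rate comparison is adjusted for baseline fall history.

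The cost is slightly more preparation by the same third party and one covariate in the model; no extra participants or staff are needed. If allocation is rolling rather than in one session, the lots should stay concealed and block sizes should vary, so that the next assignment cannot be predicted.
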